### Outcomes {12}

#### Primary outcome

The primary outcome in this study is the Quality of Recovery (QoR-15) score between anaesthesiologist-administered ultrasound-guided erector spinae block and surgeon-administered video-assisted paravertebral block at 24 h postoperative. This score is a measure of overall postoperative recovery across five dimensions of health: patient support, comfort, emotions, physical independence and pain [17].

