#### Secondary outcome measures

The following secondary outcomes will be measured:
Chronic persistent surgical pain (CPSP) after minimally invasive thoracic surgery (MITS) at postoperative day 90 (this will be achieved by assessing the patient for chronic pain by using the Brief Pain Inventory (BPI) Short Form and Short Form McGill (SF-15) questionnaires)Pulmonary function assessment ( this will be evaluated preoperatively and at postoperative days 1 and 2 using a bedside incentive spirometry)Area under the curve (AUC) of Verbal Rating Score (VRS) for pain at rest and on deep inspiration versus time over 48 hTime taken to site ESP and PVB catheterTime of administration of first intravenous opioidTotal 24- and 48-h morphine-equivalent consumptionNausea, vomiting and pruritisRegional anaesthesia block-related complications (e.g. block failure and catheter dislodgement)Duration of postanaesthesia care unit (PACU) stayLength of hospital stay and QoR-15 at 48 hSummary of postoperative complications (this will be measured by calculating the Comprehensive Complication Index (CCI) at postoperative day 30)

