The key secondary outcomes that will be measured in this trial include the following: chronic persistent surgical pain (CPSP), postoperative respiratory function, Verbal Rating Score (VRS) and measure of postoperative complications. CPSP will be assessed at postoperative day 90 by using the Brief Pain Inventory (BPI) form and Short McGill form (SF-15) questionnaires. The designated data collector will complete these questionnaires by telephone follow-up with the study participant. BPI assesses the pain intensity (scale 0–10) and interference of pain (scale 0–10) on quality of life. It was originally developed to assess cancer pain. However, it has been validated for its use in the assessment of chronic pain in the non-malignant pain population [22, 23]. The SF-15 questionnaire is a shorter version of the original McGill Pain Questionnaire. It consists of a pain rating index which has two subscales: sensory subscale with 11 words and affective subscale with 4 words. The SF-15 is a highly valid tool to evaluate pain in patients with and without neuropathic aetiology [24, 25]. Postoperative respiratory function will be assessed by measuring the patient’s average maximum inspiratory effort, by using a bedside incentive spirometer. This parameter will be gauged by the designated data collector at three time points. These time points include the preoperative period (prior to induction of general anaesthesia) and at postoperative days 1 and 2. Area under the curve (AUC) of Verbal Rating Score (VRS) for pain at rest and on deep inspiration versus time over 48 h postoperative will be measured. This method is an accepted approach for enhanced interpretation of pain outcomes for patient care [26]. Finally, the Comprehensive Complication Index (CCI) will be used to summarise the frequency and severity of all postoperative complications. This method of measuring surgical morbidity is more sensitive than existing morbidity endpoints and it is accepted as an applicable primary endpoint in surgical trials [27]. The data collectors for this trial will retrospectively review paper and electronic medical records up to postoperative day 30 and subsequently compute the CCI score according to the established Clavien-Dindo classification (available at www.assessurgery.com). The CCI score ranges between 0 (no complication) and 100 (death).

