### Statistical methods

#### Statistical methods for primary and secondary outcomes {20a}

The collected raw data will be initially inspected for any errors; this includes but is not limited to double entry errors, missing data and data that was incorrectly entered. Data will be analysed by GraphPad Prism version 8 (GraphPad, Salt Lake City, UT, USA). The data will be tested for normal distribution according to the Shapiro-Wilk test. Primary and secondary outcomes will be analysed as follows: normally distributed data will be compared between the two groups using the unpaired Student *t* test and non-normal distributed data will be compared by using the Mann-Whitney *U* test. All data will be summarised as mean ± *SD* or median (25–75% range) as appropriate, and *p* value < 0.05 will be considered statistically significant.

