#### Interim analyses {21b}

There are no interim analyses planned.

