#### Methods for additional analyses (e.g. subgroup analyses) {20b}

There are no subgroup analyses planned.

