This protocol will result in the anaesthesiologist and surgeon not being blinded to the group allocation as they will be required to perform the block. However, the primary outcome is the QoR-15 score at 24 h postoperatively which will be measured by researchers blinded to the group allocation. We have chosen to exclude patients with existing chronic pain conditions or with a history of opioid abuse. The justification for this decision comes from the fact that these patients are more likely to develop postoperative chronic pain and so the results of our 3-month chronic pain scores may be affected by the inclusion of these patients. Pain scores and quality of recovery will be recorded up to 48 h postoperatively. We acknowledge that for some patients having MITS their recovery will continue beyond 48 h; however, the acute postoperative pain following MITS is reduced by day 3 and many of our patients are discharged home at this stage. Length of stay and postoperative complications will continue to be observed after this timeframe and patients will be followed up until 3 months postoperatively. Paravertebral and ESP catheters will be placed under general anaesthesia; therefore, formal dermatomal assessment of block function will not be undertaken. Therefore, we will not be formally testing block effectiveness. However, the practice of placing these catheters under ultrasound guidance or thorascopic vision after induction of general anaesthesia is in line with common clinical practice, and therefore, our findings should still be applicable to widespread clinical practice. Patients’ preoperative QoR-15 will not be assessed in this study. Therefore, we will not have a baseline from which to compare postoperative QoR-15 scores. However, QoR-15 was designed specifically for postoperative use, and we will apply this scoring tool to both randomised cohorts equally. Moreover, the ability of QoR-15 in the immediate preoperative period to give an accurate baseline has been questioned [37]. By focusing on patient-centred outcomes in our trial design, we hope to elucidate whether these relatively straightforward fascial plane blocks can enhance recovery and improve safety for patients by reducing postoperative morbidity and complications.

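### One unadjusted p < 0.05 rule covers the primary and all secondary outcomes, so about 18 to 21 secondary comparisons can each be declared significant with no testing order, alpha allocation or exploratory label

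*Protocol article*

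**What the plan says.** All references are to the protocol article; no separate statistical analysis plan is shown.

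- **Statistical methods {20a}.** The rule opens with "Primary and secondary outcomes will be analysed as follows". It assigns a t test or a Mann-Whitney test according to the distribution of the data, and closes by stating that a p "value < 0.05 will be considered statistically significant". No outcome is exempted.
- **Primary outcome.** One is named: "The primary outcome in this study is the Quality of Recovery (QoR-15) score", at 24 h.
- **Secondary outcome measures.** A list introduced by "The following secondary outcomes will be measured" has 11 items, several of which hold more than one instrument, condition or time point.
- **Plans for assessment {18a}.** A higher tier is introduced by "The key secondary outcomes that will be measured in this trial include the following". It holds chronic post-surgical pain, respiratory function, the pain score and complications. The label has no stated consequence for testing.
- **Objectives {7}.** The hypothesis to be tested is equivalence, and it covers spirometric function and chronic pain at 3 months as well as QoR-15.
- **Interim and subgroup analyses.** "There are no interim analyses planned" ({21b}) and "There are no subgroup analyses planned" ({20b}).

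**The concern.** The rule in {20a} is something the protocol states, not a gap left for later. Followed literally, it calls every secondary difference with p below 0.05 statistically significant, with the same standing as a result on the primary outcome. With some 20 comparisons, one or more such results would be unsurprising even if the two catheters performed identically.

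The design makes this awkward. The trial sets out to show that the two techniques are equivalent. A chance result on morphine use, a pain subscale or the complication index would, by the protocol's own rule, be reported as a significant difference between them. It would then compete with the primary conclusion in the abstract and discussion of the results paper. The secondaries are also not treated as mere description, since two of them sit in the stated hypothesis and four are singled out as key.

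**Working it through.** **1. The plan's own figure.** The article's only computed figure is the sample size. Its formula is n = 2σ²(z₁₋α/₂ + z₁₋β)²/Δ², with σ = 12, Δ = 8, two-sided α = 0.05 and power 80%:

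n = 2 × 144 × (1.960 + 0.842)² / 64 = 35.3, rounded up to 36 per group.

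This matches the stated 36 (40 enrolled). The full 0.05 is assigned to one comparison, QoR-15 at 24 h. With one primary, one time point and no interim look, secondary testing cannot inflate that error rate.

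**2. Counting the secondary comparisons** (from the secondary outcome list):

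| Item | Lower count | Upper count |
|---|---|---|
| BPI | 1 | 2 (intensity, interference) |
| Short-form McGill | 1 | 2 (sensory, affective) |
| Spirometry, days 1 and 2 | 2 | 2 |
| Pain-score AUC, rest and deep inspiration | 2 | 2 |
| Catheter siting time | 1 | 1 |
| Time of first intravenous opioid | 1 | 1 |
| Morphine equivalents, 24 h and 48 h | 2 | 2 |
| Nausea, vomiting, pruritus | 3 | 3 |
| Block-related complications | 1 | 2 (failure, dislodgement) |
| PACU stay | 1 | 1 |
| Hospital stay | 1 | 1 |
| QoR-15 at 48 h | 1 | 1 |
| Comprehensive Complication Index | 1 | 1 |
| **Total** | **18** | **21** |

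**3. Chance of at least one false significant result, assuming no outcome truly differs.**

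For k independent tests the rate is 1 − 0.95^k:

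- k = 18: 1 − 0.95¹⁸ = 0.603
- k = 21: 1 − 0.95²¹ = 0.659

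For tests with a common correlation ρ, write each statistic as √ρ·U + √(1−ρ)·E, with U shared and E separate, both standard normal. The rate is then one minus the average over U of the probability that all k statistics lie within ±1.96. The documents give no correlation, so ρ is an assumption and a range is shown:

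| k | ρ = 0 | ρ = 0.3 | ρ = 0.5 | ρ = 0.7 | ρ = 0.8 |
|---|---|---|---|---|---|
| 18 | 0.603 | 0.508 | 0.398 | 0.277 | 0.216 |
| 21 | 0.659 | 0.555 | 0.429 | 0.296 | 0.228 |

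A common correlation across all outcomes is itself generous to the plan, because it links siting time, pruritus and hospital stay as closely as two pain scores. With 21 tests correlated only within related domains, the rate is 0.62 at a within-domain correlation of 0.5 and 0.57 at 0.8.

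The expected number of false positives does not depend on correlation: 18 × 0.05 = 0.90 and 21 × 0.05 = 1.05.

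**4. The four key secondaries alone.** One independent test each gives 1 − 0.95⁴ = 0.185. Unpacked into 9 tests (two BPI, two McGill, two spirometry, two AUC, one complication index), the rate is 0.370 if independent, 0.269 at ρ = 0.5 and 0.165 at ρ = 0.8.

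**5. A stricter count.** Take the lower count of 18. Remove siting time, where a real difference is plausible, and the four items that may be recorded yes/no (nausea, vomiting, pruritus, block complications), where exact tests in small groups usually reject less often than 5%. This leaves 18 − 5 = 13 tests, and 1 − 0.95¹³ = 0.487 if independent. At ρ = 0.5 and 0.8 even 12 tests give 0.320 and 0.185.

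**The case against.** The strongest objection is scope. Adjustment for multiple secondary outcomes is commonly left to the analysis plan, which is not shown, so the absence of a correction is not a fault in itself. That is right as far as it goes. But {20a} is not silent: it fixes a significance rule and extends it expressly to secondary outcomes. A later plan that labelled them exploratory would have to depart from the protocol. What remains is a point about the rule as written.

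The count and the assumption of no true differences can also be challenged. Both come from unpacking the list, and siting time probably does differ, since one catheter is placed under ultrasound by an anaesthesiologist and the other by a surgeon under thoracoscopic view. This stands, and the stricter count in step 5 allows for it. The rate falls but stays several times 0.05.

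Some stronger readings are tempting but not supported:

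- *That the trial's main conclusion is compromised.* It is not by this route. There is one primary outcome, with no interim and no subgroup analysis, and no section makes success depend on a secondary.
- *That spirometry and chronic pain are co-primary because the objectives include them.* The primary outcome section names QoR-15 at 24 h only.
- *That the outcomes have no hierarchy.* There is a primary, a key tier and a longer list. What is missing is a testing order or alpha allocation among the secondaries.
- *That the false-positive chance is a fixed 40%.* That figure needs a common correlation near 0.5, which the documents do not give.
- *That the Discussion rests a safety claim on the complication index.* The sentence asking whether the blocks "can enhance recovery and improve safety for patients by reducing postoperative morbidity and complications" is worded as a hope to find out. It names neither the index nor a p-value rule.

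Finally, a false difference is not the type I error of an equivalence claim. That is correct. The rates above measure the risk of spurious claims of difference, which is what the rule in {20a} invites.

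**Conclusion.** The point holds as a defect in a stated rule, limited to how secondary results are declared. Section {20a} would call any of about 18 to 21 secondary differences significant at an unadjusted 0.05. If none truly differs, at least one false declaration has a probability of about 60 to 66% under independence, 40 to 43% at a common correlation of 0.5 and 22% at 0.8, with about one expected in all cases. These figures rest on my unpacking of the list, full 5% rejection for each test, and an assumed correlation. They are less certain than the qualitative conclusion, which survives the stricter count.

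The primary type I error and the sample size of 36 per group (40 enrolled) are untouched. This is a cheap and worthwhile correction of wording, not a threat to the trial's main analysis.

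**What to change.** In {20a}, replace the single significance sentence with two statements.

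1. The confirmatory claim is confined to QoR-15 at 24 h and is judged by a criterion that fits the equivalence hypothesis: the confidence interval for the between-group difference, at a stated level, set against the 8-point limit in the sample size section. Simply restricting the p < 0.05 rule to the primary would entrench a test of difference as the decision rule of an equivalence trial.
2. Secondary outcomes are exploratory. They are reported as between-group estimates with 95% confidence intervals and are not declared statistically significant.

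If claims on the four key secondaries are wanted, name one measure and one time point for each and apply Holm's procedure at 0.05 across the four. The ordered p values are then compared with 0.05/4 = 0.0125, 0.05/3 = 0.0167, 0.05/2 = 0.025 and 0.05, stopping at the first failure. The remaining secondaries stay exploratory. If the claim sought on a key secondary is equivalence, it also needs its own margin.

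The cost is a few sentences in the protocol and analysis plan, with no new data or patients. The one loss is that an isolated secondary result just under 0.05 can no longer be called significant.

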#### Interim analyses {21b}

There are no interim analyses planned.

#### Methods for additional analyses (e.g. subgroup analyses) {20b}

There are no subgroup analyses planned.

#### Methods in analysis to handle protocol non-adherence and any statistical methods to handle missing data {20c}

The primary outcome will be assessed using an unpaired Student *t* test analysis or Mann-Whitney *U* test, depending on data distribution. Given our expectation that very few patients will be lost to follow-up during their inpatient stay and protocol adherence strategies as mentioned above, we expect missing data will be reduced to a minimum when analysing the primary outcome. If a statistical method is needed to account for missing data in the secondary outcomes (e.g. CPSP survey at 3-month follow-up), multiple imputation will be used.

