### Objectives {7}

Our main aim and corresponding hypotheses are outlined below.

We will conduct a randomised controlled clinical trial comparing the efficacy of anaesthesiologist-administered, ultrasound-guided ESP catheter analgesia to surgeon-administered, video-assisted PVB catheter analgesia. We will test the hypothesis that anaesthesiologist-administered ultrasound-guided ESP catheter analgesia is equivalent to surgeon-administered, video-assisted PVB catheter analgesia, in terms of early Quality of Recovery (QoR-15) and postoperative respiratory spirometric function at 24–48 h and CPSP at 3 months after MITS surgery.

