### Trial design {8}

This manuscript outlines a research protocol for a double-blind, randomised controlled, equivalence trial. This study is designed as equivalence, as the analgesic effectiveness of a successful paravertebral block is not questioned. Patients that volunteer to participate in this clinical trial will be equally (1:1) and randomly allocated into one of two intervention groups: anaesthesiologist-administered ultrasound-guided erector spinae catheter group (ESP catheter group) or surgeon-administered, video-assisted paravertebral block catheter group (PVB group). Figure 1 illustrates the study flow chart. Recruitment commenced on 12 May 2021, and it is expected to take between 9 and 12 months for completion.

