### Sample size {14}

The established minimum clinically important difference (MCID) in QoR-15 score after surgery is 8.0 [18], and the *SD* of QoR-15 scores is typically between 10 and 16 [range of QoR score is 1–150]. Therefore, we considered a reduction in mean QoR-15 scores by 8 to be clinically meaningful and used this value as our delta (Δ) limit. In addition, we have chosen a standard deviation (*SD*) of 12 to reflect our study population. Based on these assumptions, we considered the following for our sample size analysis. For a two-sided test, assuming a type I error (*α*) = 0.05 and type II error (*β*) = 0.2, a sample size of *n* = 36 per group will have 80% power to detect a statistically significant difference in mean QoR-15 scores.

We aim to enrol *n* = 40 each group to allow for loss to follow-up, missing data or withdrawal of consent. The sample size was estimated using the following formula [19]: *n* = 2*σ*^2^ (*z*1 − *α*/2 + *z*1 − *β*)^2^/Δ^2^, where *α* and *β* are the probabilities of type I and II errors, *σ* is the *SD* and Δ is the delta limit. This calculation was subsequently verified by an online calculator (Georgiev G.Z., “*Sample Size Calculator*”, Available at: https://www.gigacalculator.com/calculators/power-sample-size-calculator.php).

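### Equivalence is declared with an 8-point limit, but the only primary analysis is a test of no difference that never uses the limit and cannot establish equivalence

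*Protocol article*

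**What the plan says.** All references are to the protocol article.

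- **Objectives {7}** states the hypothesis: "We will test the hypothesis that anaesthesiologist-administered ultrasound-guided ESP catheter analgesia is equivalent to surgeon-administered, video-assisted PVB catheter analgesia", with early QoR-15 as the first outcome named.
- **Trial design {8}** confirms the framework: "This study is designed as equivalence, as the analgesic effectiveness of a successful paravertebral block is not questioned".
- **Sample size {14}** sets the limit: "we considered a reduction in mean QoR-15 scores by 8 to be clinically meaningful and used this value as our delta (Δ) limit". It takes an SD "of 12 to reflect our study population", from a typical range of 10 to 16. The calculation is then framed as follows: "For a two-sided test, assuming a type I error (*α*) = 0.05 and type II error (*β*) = 0.2". The result is 36 "per group will have 80% power to detect a statistically significant difference in mean QoR-15 scores", raised to 40 per group for losses.
- **Statistical methods {20a}** compares the groups with an unpaired t test or a Mann-Whitney U test, depending on a Shapiro-Wilk test, where a p "value < 0.05 will be considered statistically significant".
- **Section {20c}** repeats this for the primary outcome: "The primary outcome will be assessed using an unpaired Student" t test or a Mann-Whitney U test.

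The 8-point limit appears only in the sample size section. No section compares a confidence interval with it, describes two one-sided tests, or gives any other rule for concluding equivalence.

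**The concern.** An equivalence trial has to reject the hypothesis that the true difference is as large as the limit. The planned tests instead reject, or fail to reject, the hypothesis that the difference is zero. Failing to reject zero says nothing about whether a difference of 8 points has been excluded, and noisier data make that failure more likely.

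This is the primary outcome and the trial's central claim. Followed as written, the plan yields a p value that does not bear on the stated hypothesis. Whoever reports the trial then has no prespecified route to the conclusion that the trial was set up to reach. The obvious improvised route, treating non-significance as equivalence, carries an uncontrolled error rate.

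**Working it through.** **Inputs.** From Sample size {14}: limit Δ = 8, SD σ = 12 (range 10 to 16), two-sided α = 0.05, power 80%, n = 36 evaluable and 40 enrolled per group. Two inputs are my assumptions, because the article gives neither: the level of the equivalence test (both usual levels are shown) and a true difference of 0 for equivalence power.

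**1. The plan's own figure.** n = 2σ²(z₀.₉₇₅ + z₀.₈)²/Δ² = 2 × 144 × (1.960 + 0.842)²/64 = 35.3, rounded up to 36. This reproduces the stated sample size. It is the formula for detecting a difference, so sections {14}, {20a} and {20c} agree with each other and conflict with {7} and {8}.

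**2. Non-significance at a true 8-point difference.** The t statistic is non-central t with 2n − 2 degrees of freedom and non-centrality 8/(σ√(2/n)). At n = 36 and σ = 12 the standard error is 12 × √(2/36) = 2.83, so the non-centrality is 2.83. The probability of p > 0.05 is:

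| SD | n = 36 per group | n = 40 per group |
|---|---|---|
| 10 | 8% | 6% |
| 12 | 20% | 16% |
| 16 | 45% | 40% |

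Two one-sided tests against ±8 would hold the error at the limit to 5% (90% CI) or 2.5% (95% CI), whatever the SD.

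**3. The same data under both rules (n = 36, observed SD 12).**

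- Largest non-significant observed difference: 1.994 × 2.83 = 5.64.
- Upper 95% limit at that difference: 5.64 + 5.64 = 11.3. Upper 90% limit: 5.64 + 1.667 × 2.83 = 10.4. Both lie well beyond 8.
- Equivalence would require an observed difference below 8 − 1.667 × 2.83 = 3.3 (90% CI) or 8 − 5.64 = 2.4 (95% CI).

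Observed differences between about 3.3 (or 2.4) and 5.6 are therefore non-significant without showing equivalence.

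**4. Power for equivalence (true difference 0, SD 12).** The normal approximation is 2Φ(8/SE − z) − 1. At n = 36 with a 90% CI: 8/2.83 − 1.645 = 1.18, which gives 76%. Exact t-based values:

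| CI | n = 36 | n = 40 | n per group for 80% |
|---|---|---|---|
| 90% (one-sided 5% each) | 75% | 81% | 40 |
| 95% (one-sided 2.5% each) | 59% | 68% | 49 |

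Over SD 10 to 16 the number needed per group runs from 28 to 70 (90% CI) and from 34 to 86 (95% CI).

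**The case against.** **Nothing says that non-significance means equivalence.** This is correct. A reader might infer from the text that p > 0.05 will be reported as equivalence, but section {20a} only says what counts as statistically significant. The error rates in step 2 therefore apply only if that reading is adopted. The point survives, because without that reading the protocol has no criterion at all for its own hypothesis.

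**An analysis plan could supply the criterion.** That would answer a silence, but the article is not silent. It names the primary test and the threshold, and an equivalence analysis elsewhere would contradict that text.

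**The opposite harm is tempting but not supported.** A reader might argue that a small real difference would come out significant and equivalence would be wrongly denied: at n = 36 and SD 12, a true 4-point difference gives p < 0.05 in 29% of trials. The confidence-interval rule would not rescue those trials. With an observed SD of 12, significance needs at least 5.64 points and equivalence needs less than 3.3 (90% CI), so the two cannot occur together. Allowing the observed SD to vary, they coincide in about 0.01% of trials.

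**Differences short of the limit do not show an error.** A true 6-point difference is non-significant in 45% of trials at n = 36 and SD 12, but 6 lies inside the limit, so calling it equivalent would be true by the trial's own standard. Only the error at the limit counts here.

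**The limit may not be two-sided.** Section {14} speaks of a reduction of 8. A range of −8 to +8 is the natural reading for an equivalence trial, but the sponsor has to confirm it.

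**Conclusion.** The point holds as a contradiction within the document. Equivalence is the stated hypothesis and design, and 8 points is the stated limit, but the stated primary analysis tests for no difference, never uses the limit, and cannot establish equivalence.

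If non-significance were taken as equivalence, a true difference at the limit would pass in 16% to 20% of trials at the planned SD, and in 40% to 45% at the top of the protocol's SD range, against 5% or 2.5% under an equivalence test. These figures assume normal data with equal SDs and 36 to 40 evaluable patients per group.

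The stated 80% power is for detecting a difference and does not carry over. Power for equivalence depends on the CI level chosen, and the figures above also assume a true difference of exactly 0. With a 90% CI, reaching 80% takes all 40 patients per group and leaves nothing for losses. The documents do not show that the trial will misreport non-significance as equivalence, only that no valid rule is in place. The point must be fixed, because it concerns the primary conclusion.

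**What to change.** In sections {20a} and {20c}, replace the primary analysis with text to this effect:

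> The primary analysis estimates the mean difference (ESP minus PVB) in QoR-15 at 24 h with its confidence interval, whatever the Shapiro-Wilk result. Equivalence is concluded only if the whole interval lies within −8 to +8. If it does not, equivalence has not been shown. A p value above 0.05 is not evidence of equivalence.

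Three matters go with it:

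- **CI level.** Fix one level in advance: 90% (two one-sided 5% tests) or 95%. They are not interchangeable, as the power table shows.
- **Limit and skewed data.** The sponsor should confirm that the limit is symmetric. The Mann-Whitney test should not serve as the primary analysis, since it has no link to a limit on the mean difference. If the data are skewed, a bootstrap CI for the mean difference could serve as a check.
- **Sample size {14}.** Restate the power for equivalence at the chosen level, with the assumed true difference and SD: about 75% at 36 and 81% at 40 per group with a 90% CI, or about 59% and 68% with a 95% CI.

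**Cost.** The change is to wording and stated power, and no new data are needed. The criterion is stricter than non-significance and the stated power becomes less favourable, particularly with a 95% CI, for which about 49 evaluable patients per group would be needed to reach 80%. The wording should be settled before unblinding.
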